#### Control arm: intravenous artesunate only

This arm will receive intravenous artesunate at 3 mg/kg if weight is less than 20 kg or 2.4 mg/kg if weight is greater than 20 kg at 0, 12, and 24 h and subsequently a daily dose of 1.2 mg/kg/day until conscious. Additionally, intravenous 10% dextrose water will be given in lieu of intravenous quinine.

#### All the groups

The two groups will receive enteral artemisinin-based combination therapy (ACT) as soon as they regain consciousness and can tolerate the full course of oral ACT in line with WHO recommendation.

#### Criteria for discontinuing or modifying allocated interventions {11b}

Participants who regained full recovery after initial treatment.Participants who also wish to exit after due counselling.Participants with intractable hypoglycaemia despite maintenance at 12.5% glucose.Participants with dysrhythmias will be unblinded.Participants who develop commodities of severe malaria that could confound the measurable outcomes such as uraemic encephalopathy.Participant with a new disease besides cerebral malaria or updated clinical history related to exclusion criteria.

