**Methods:**

This is a parallel multi-site randomized controlled superiority triple blinded trial consisting of intravenous artesunate plus quinine and a control arm of intravenous artesunate only. Eligible and assenting children aged 6 months to 17 years will be recruited from 4 tertiary hospitals by random selection from the list of tertiary hospitals in Nigeria. Participants will be randomized and assigned in parallel into two arms using random numbers generated from GraphPad Prism (version 9) by a clinical pharmacologist who has no link with the investigators, the patients, or the statistician. The primary measurable outcome is survival at 12, 24, and 48 h post-randomization. A composite secondary outcome consists of the number of children that regained consciousness, parasitaemia and defervescence at 12 and 24 h post-randomization and haematological and inflammatory markers at 24 and 48 h post-randomization. Adverse events both solicited and unsolicited are recorded all through the study post-randomization. The study is approved by the State Research Ethics Review Committee. Data analysis will be performed in GraphPad Prism version 9.

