### Outcomes {12}

#### The primary outcome

The primary outcome is survival measured at 48 h post-randomization.

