#### Secondary outcomes

Number of patients that regained full consciousness as measured by GCS/MGCS of > 11 for children > 5 years or Blantyre Coma Scale of > 3 in children < 5 years at 12 and 24 h post-randomization.Number of patients with asexual form of malaria parasite present or absent at 12 and 24 h post-randomization.Number of patients that achieved fever defervescence (attainment and sustenance of axillary temperature of < 37.5 °C) at 12 and 24 h post-randomization.Parasite density at 12 and 24 h post-randomization.Number of patients with neurologic deficits at the fourth week (day 29) post-intervention in each of the arms. Neurology deficit is defined as the presence of impaired cognitive, motor or cranial nerve palsy and or persistence of convulsions.Time to convert to a full dose of enteral artemisinin-based combination therapy.The side effect profile (adverse events and serious adverse events) of medication in each arm of study: (i) solicited side effects include hypoglycaemia, arrhythmia, thrombocytopenia, tinnitus and anaemia; (ii) unsolicited adverse events as reported by patients post-randomization; (iii) random plasma glucose will be measured 6 hourly until 48 h after parasite clearance. Hypoglycaemia will be corrected with 2-4 ml/kg of 10% D/W and maintenance with glucose infusion at 6–8 mg/kg/min until euglycaemic; (iv) electrocardiography will be recorded before the administration of anti-malaria and 4 h after an intervention. The QT and RR will be measured by software and checked manually. Bazett’s formula will be used to correct the QT interval (QTc = QT/RR**0.5). Prolonged QT interval managed as per hospital protocol; (v) haematocrit, serum ferritin, platelet count and erythrocyte sedimentation rate will be monitored at baseline and 24 h and 48 h post-randomization.Plasma levels of inflammatory markers including C reactive protein, procalcitonin, lactate dehydrogenase and interleukin 6 at baseline, 24 h, and 48 h. Inflammatory markers and cytokine are included to assess a possible ‘cytokine storm’ in the course of parasite clearance.

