### Methods in analysis to handle protocol non-adherence and any statistical methods to handle missing data {20c}

The result of the study will be analysed per protocol. The number of participants with missing data will be clearly stated, and the missing items will be mentioned.

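### Only a per-protocol analysis is named for a superiority trial of 48 h survival; the primary analysis should include every randomised child in the allocated arm

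*Protocol article*

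**What the plan says.** The abstract gives the design: "This is a parallel multi-site randomized controlled superiority triple blinded trial". The outcomes section sets the endpoint: "The primary outcome is survival measured at 48 h post-randomization".

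The only statement on the analysis set is in {20c}, under the heading for protocol non-adherence and missing data: "The result of the study will be analysed per protocol". That section adds that the extent of missing data will be reported. It does not define the per-protocol set, and no other section names an intention-to-treat or all-randomised analysis.

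Section {11b} lists the reasons for discontinuing or modifying the allocated intervention. Three of them matter here:
- "Participants who develop commodities of severe malaria that could confound the measurable outcomes such as uraemic encephalopathy" (the second noun is probably a misprint for comorbidities);
- "Participants with intractable hypoglycaemia despite maintenance at 12.5% glucose";
- dysrhythmia, for which the child is unblinded.

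The safety part of the secondary outcomes overlaps with this list: "solicited side effects include hypoglycaemia, arrhythmia, thrombocytopenia, tinnitus and anaemia". The arms differ in what could produce such events. Only the dual arm receives quinine; in the control arm "intravenous 10% dextrose water will be given in lieu of intravenous quinine".

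**The concern.** In a superiority trial, randomisation protects the comparison only while children are analysed in the arm to which they were allocated. A per-protocol set selects children by what happened after allocation. Several reasons in {11b} are events of that kind. They may mark a worse prognosis, or they may result from the study drugs.

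The wording of the first criterion quoted points the same way. A complication that arises after randomisation does not confound a randomised comparison. It may be a consequence of treatment or a step towards death, so excluding such children would remove part of the outcome being compared.

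If excluded children die at a different rate from the others, and exclusion is more frequent in one arm, the difference in 48 h survival is distorted. Blinding does not prevent this where the drugs themselves cause different complications.

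**Working it through.** **Inputs from the protocol article.** Sample size section: 23.0% v 12.5%, 80% power, two-sided 0.05, 10% attrition, 470 in total, 235 per arm. Statistical methods section: chi-squared or Fisher's exact test for categorical outcomes.

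**Inputs assumed.** The share removed per arm (r) and the mortality among removed children (m). The article gives neither.

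**Step 1: the plan's own figure.** The pooled two-proportion formula, with mean rate 0.1775, gives

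n = [1.960 × √(2 × 0.1775 × 0.8225) + 0.842 × √(0.23 × 0.77 + 0.125 × 0.875)]² / 0.105² = 207 per arm, or 414 in total.

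414 / 0.90 = 460, within 3% of the stated 470. The 235 per arm is therefore a fair basis for what follows.

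**Step 2: mortality among the children who are kept.** With p the mortality of all randomised children in an arm,

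kept mortality = (p − r × m) / (1 − r).

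Two consequences follow when the true mortality p is the same in both arms:
- If r and m are equal in both arms, kept mortality is equal, so the difference is unbiased.
- If m = p, that is, removal is unrelated to death, kept mortality is p in each arm, whatever the removal shares.

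Bias therefore needs removal that both differs by arm and is related to death.

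**Step 3: illustration with no true effect.** Set p = 0.23 in both arms, r = 0.05 in control and 0.10 in dual therapy. About 223 control and 212 dual children are kept.
- m = 0.60: control (0.23 − 0.03)/0.95 = 21.05%; dual (0.23 − 0.06)/0.90 = 18.89%; difference 2.16 points in favour of dual.
- m = 0.40: control (0.23 − 0.02)/0.95 = 22.11%; dual (0.23 − 0.04)/0.90 = 21.11%; difference 0.99 points.
- m = 0.23: 23.0% in both; difference 0.

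**Step 4: chance of a false finding in favour of dual therapy.** Use the pooled z test (equivalent to the uncorrected chi-squared test) at two-sided 0.05. For m = 0.60 the overall kept rate is about 0.200, so the standard error is √(0.200 × 0.800 × (1/223 + 1/212)) = 0.0384. The shift is 0.0216/0.0384 = 0.56 standard errors, and the chance of exceeding 1.96 is 1 − Φ(1.96 − 0.56) = 8.1%.

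| Removed, control v dual | Mortality among removed | Kept mortality, control v dual | Difference in favour of dual | False 'dual better' |
|---|---|---|---|---|
| 5% v 5% | 60% | 21.1% v 21.1% | 0 | 2.5% |
| 5% v 10% | 23% | 23.0% v 23.0% | 0 | 2.5% |
| 5% v 10% | 40% | 22.1% v 21.1% | 1.0 point | 4.4% |
| 5% v 10% | 60% | 21.1% v 18.9% | 2.2 points | 8.1% |
| 10% v 5% | 60% | 18.9% v 21.1% | −2.2 points | 0.6% |

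A simulation of 200,000 trials gave the same 2.5%, 4.4% and 8.1% for the three rows with 5% v 10% removed. The last row shows that the direction depends on which arm loses more children.

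**The case against.** The strongest reply is that the two sections are not linked in the text. Section {11b} governs the drug. It does not say that anyone leaves follow-up or analysis. A child who stops under a rule written in the protocol has arguably followed the protocol, so a per-protocol set could keep that child. The participant timeline schedules survival with no exception for children off treatment, and the definition of the set may stand in a fuller document. All of this stands: exclusion of these children is possible, not stated. It does not answer the main point. The choice of a per-protocol analysis is itself stated, under the non-adherence heading, and no all-randomised analysis stands beside it.

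The arm imbalance is also only partly documented. Hypoglycaemia and arrhythmia are solicited in both arms and are not attributed to quinine there. Uraemic encephalopathy is tied to neither drug. More removals in the dual arm is an assumption.

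Some stronger readings are tempting, but the article does not support them:
- **Recovered children are dropped.** A reader might infer this from "Participants who regained full recovery after initial treatment". But both groups move to oral combination therapy once conscious, so stopping on recovery is the planned course for most survivors. No sensible per-protocol set would exclude them.
- **Power is lost.** At the planned rates, removing 10% of control and 5% of dual children, 60% of them dying, lowers power from 84.8% to 75.3%. But removal unrelated to death already gives 82.0% through smaller numbers alone. With the shares reversed, power rises to about 99%. No general statement about power follows.
- **The criterion on confounding complications must go, or supportive care is restricted.** Once all randomised children are analysed, that criterion no longer threatens the comparison. The section on concomitant care does not say that care is withheld, and it removes nobody from the analysis.

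**Conclusion.** The point holds as a poor choice of analysis set in {20c}: a superiority trial with 48 h survival as primary outcome should not rest on a per-protocol analysis alone. Section {11b} supplies examples of children whom such a set could exclude. It is not evidence that they will be excluded.

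The size and direction of any bias are unknown. The 1.0 to 2.2 points and the 4.4% to 8.1% (against 2.5%) rest on assumed removal of 5% v 10% and assumed mortality of 40% to 60% among removed children. They also use 23% mortality in both arms; the sample size section attaches that rate to quinine monotherapy, not to the artesunate control. With no true effect, there is no between-arm bias if removal and mortality among the removed are equal in both arms, or if removal is unrelated to death. A reader might infer that the plan is built to favour dual therapy; the article does not show this, since unequal removal could act either way.

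**What to change.** - **{20c}:** make the primary analysis of 48 h survival include every randomised child in the allocated arm, whatever treatment was received. Keep per-protocol as a sensitivity analysis.
- **{11b}:** state that a child who stops the allocated treatment stays in follow-up for survival and for the day 29 neurological outcome, unless consent for follow-up is withdrawn.

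This changes wording only. It needs no extra patients or visits: the timeline already schedules survival at 12, 24, 48 and 72 h and a neurological examination at 29 days. The cost is some dilution of the treatment effect by children who stop early. Children whose caregivers withdraw consent for follow-up before 48 h may still lack the outcome and should be reported by arm.

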#### Strategies to improve adherence to interventions {11c}

Prior to recruitment, parents/caregivers of study participants will be educated on the complication of severe malaria to gain their support in the research.All study participants will enjoy social support throughout the hospital stay.The possible side effect profile of artesunate and quinine will be discussed with the parents/caregivers at the enrolments for the study.The study will only be responsible for the trial cost. This would include the cost of medications for the intervention, cost of managing adverse events from the intervention and the primary laboratory tests needed for the diagnosis of the disease in line with research ethics. Other costs will be the responsibility of the caregivers of the patients.

#### Relevant concomitant care permitted or prohibited during the trial {11d}

Concomitant treatment for septicaemia, severe anaemia, AKI stages 1 and 2 and hypoglycaemia will be permitted.Treatments for other comorbidities of severe malaria which do not confound the protocol and measured outcomes will be permissible.

#### Provisions for post-trial care {30}

The participants with neurologic deficit as a result of the disease will be followed up by the paediatric neurologist for a continuum of care.

### Outcomes {12}

#### The primary outcome

The primary outcome is survival measured at 48 h post-randomization.

#### Secondary outcomes

Number of patients that regained full consciousness as measured by GCS/MGCS of > 11 for children > 5 years or Blantyre Coma Scale of > 3 in children < 5 years at 12 and 24 h post-randomization.Number of patients with asexual form of malaria parasite present or absent at 12 and 24 h post-randomization.Number of patients that achieved fever defervescence (attainment and sustenance of axillary temperature of < 37.5 °C) at 12 and 24 h post-randomization.Parasite density at 12 and 24 h post-randomization.Number of patients with neurologic deficits at the fourth week (day 29) post-intervention in each of the arms. Neurology deficit is defined as the presence of impaired cognitive, motor or cranial nerve palsy and or persistence of convulsions.Time to convert to a full dose of enteral artemisinin-based combination therapy.The side effect profile (adverse events and serious adverse events) of medication in each arm of study: (i) solicited side effects include hypoglycaemia, arrhythmia, thrombocytopenia, tinnitus and anaemia; (ii) unsolicited adverse events as reported by patients post-randomization; (iii) random plasma glucose will be measured 6 hourly until 48 h after parasite clearance. Hypoglycaemia will be corrected with 2-4 ml/kg of 10% D/W and maintenance with glucose infusion at 6–8 mg/kg/min until euglycaemic; (iv) electrocardiography will be recorded before the administration of anti-malaria and 4 h after an intervention. The QT and RR will be measured by software and checked manually. Bazett’s formula will be used to correct the QT interval (QTc = QT/RR**0.5). Prolonged QT interval managed as per hospital protocol; (v) haematocrit, serum ferritin, platelet count and erythrocyte sedimentation rate will be monitored at baseline and 24 h and 48 h post-randomization.Plasma levels of inflammatory markers including C reactive protein, procalcitonin, lactate dehydrogenase and interleukin 6 at baseline, 24 h, and 48 h. Inflammatory markers and cytokine are included to assess a possible ‘cytokine storm’ in the course of parasite clearance.

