**Assessments**							
Electrocardiograhy	x	x	x	x	x		
*Survival*		x	x	x	x		
*Regained consciousness*		x	X				
*Parasitaemia*		X	X			.	
*Defervescence*		X	X				
*Adverse events*	x	x	x	x	x	x	x
*Haematological indices*	x		x	x			
*Inflammatory markers*	x		x	x			
*Glucose monitoring*	x	x	x	x	x	x	

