### Statistical methods for primary and secondary outcomes {20a}

Data from this study will be analysed using the GraphPad Prism 9 (GraphPad Software, [name]). The appropriate descriptive statistics will be used to present the socio-demographic characteristics of study participants. The comparison of categorical outcomes between the arms will be analysed using the chi-squared or Fisher’s exact tests, as appropriate, and presented as risk differences, risk ratios, and 95% confidence intervals. Kaplan-Meier analysis and Cox regression models will be used to compare the recovery of consciousness, defervescence, and survival.

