#### Adverse event reporting and harms {22}

All participants in this trial will be monitored for medication side effects and adverse events. An adverse event (AE) is any untoward medical occurrence which happens to a participant on a trial. All AEs will be reported in the case report form (CRF) regardless of suspected causality. Medidata rave will be used for reporting of AEs. Serious adverse events (SAEs) include fatal medical occurrences, life-threatening, that require or prolong hospitalization or cause congenital anomaly or permanent or significant disability or incapacity. All SAEs will be reported to the sponsor, Local Health Research Ethics and DSMB, and Trial Steering Committee within 24 h.

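### Anaemia, thrombocytopenia and hypoglycaemia are listed as medication side effects with no rule using the 0 h values already measured, so abnormality present at entry can be counted in both arms

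*Protocol article*

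**What the plan says.** All references are to the protocol article.

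- **Outcomes {12}, Secondary outcomes.** One outcome is "The side effect profile (adverse events and serious adverse events) of medication in each arm of study". Under it, "solicited side effects include hypoglycaemia, arrhythmia, thrombocytopenia, tinnitus and anaemia". No threshold, grade, or new-onset or worsening condition is attached.
- **Same item, monitoring.** "haematocrit, serum ferritin, platelet count and erythrocyte sedimentation rate will be monitored at baseline and 24 h and 48 h post-randomization", and "random plasma glucose will be measured 6 hourly until 48 h after parasite clearance". In the Participant timeline {13}, the row "Glucose monitoring" and the haematology row are both marked at 0 h, so an entry value is scheduled for all three conditions.
- **Adverse event reporting and harms {22}.** An adverse event is any untoward occurrence in a trial participant. Onset or worsening after treatment is not required. "All AEs will be reported in the case report form (CRF) regardless of suspected causality".
- **When adverse events are recorded.** The timeline marks them at every time point, including 0 h. The abstract (Methods) places recording after randomization.
- **Who is enrolled.** Relevant concomitant care {11d} permits treatment of severe anaemia and hypoglycaemia and goes on to speak of other comorbidities of severe malaria. None of the three conditions is an exclusion criterion.
- **Analysis {20a}.** Categorical outcomes are compared between arms by chi-squared or Fisher's exact test, "presented as risk differences, risk ratios, and 95% confidence intervals". No baseline value enters.
- **Interim analyses {21b}.** Early-stopping consideration is tied to adverse events exceeding 50%.

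**The concern.** Reporting every adverse event whatever its cause is sound practice. The difficulty lies in the next step, where the outcome presents these conditions as side effects of medication and compares them between arms. A child who arrives anaemic or with a low platelet count and is still so at 24 h meets the label without any drug effect. Such children are expected in both arms and add the same amount to each arm's count.

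The trial adds quinine to artesunate, and one of its stated objectives is the side effect profile of the two treatments. For a harm outcome, dilution towards no difference is the unsafe direction. The side-effect percentages would also be too high to read as drug effects, and the percentage used when early stopping is considered would rise for reasons unrelated to treatment.

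**Working it through.** **The plan's own figure.** The document computes nothing for side effects. The only input taken from it is the arm size, 470 / 2 = 235 (Sample size {14}). That total reproduces closely: 23.0% versus 12.5%, two-sided 5%, 80% power, pooled variance, gives 207 per arm; 207 / 0.90 = 230 per arm, or 460. This is within 3% of 470. The point below does not depend on it.

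**Assumptions.** The document gives neither prevalence at entry nor incidence.
- *b*: share already abnormal at 0 h and still abnormal when counted, equal in the two arms on average because of randomization.
- *q*: new-onset risk among children normal at 0 h, 10% in the control arm and 25% in the dual arm. A milder contrast of 10% versus 20% follows.

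**Formulas.**
- Risk if every abnormality counts: *b* + (1 − *b*)*q*.
- New onset per randomized child: (1 − *b*)*q*.
- Power = Φ[(|p1 − p2| − 1.96·SE0) / SE1], where SE0 uses the pooled proportion and SE1 the two separate proportions.

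**Example, b = 30%.**
- Counted risks: 0.30 + 0.70 × 0.10 = 37% and 0.30 + 0.70 × 0.25 = 47.5%.
- Risk ratio: 47.5 / 37 = 1.28, against 25 / 10 = 2.5 in children normal at 0 h.
- Power with 235 per arm: SE0 = √(0.4225 × 0.5775 × 2/235) = 0.0456 and SE1 = √[(0.37 × 0.63 + 0.475 × 0.525)/235] = 0.0453. Then (0.105 − 1.96 × 0.0456)/0.0453 ≈ 0.35, or 64%.
- Children normal at 0 h only: 235 × 0.70 = 164.5 per arm, 10% versus 25%, power 95%.
- New onset over all randomized: 7% versus 17.5%, 235 per arm, power 94%.
- Risk difference: 47.5 − 37 = 10.5 points; new onset per randomized child 17.5 − 7 = 10.5 points. They are the same.

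**Range, 10% versus 25%.**

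| b | All counted | RR | Power | Power, normal at 0 h only (RR 2.5) | Power, new onset over all randomized |
|---|---|---|---|---|---|
| 30% | 37% vs 47.5% | 1.28 | 64% | 95% | 94% |
| 50% | 55% vs 62.5% | 1.14 | 38% | 86% | 82% |
| 70% | 73% vs 77.5% | 1.06 | 20% | 65% | 59% |

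**Milder contrast, 10% versus 20% (RR 2.00 in children normal at 0 h).**

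| b | All counted | RR | Power | Power, normal at 0 h only |
|---|---|---|---|---|
| 20% | 28% vs 36% | 1.29 | 46% | 78% |
| 40% | 46% vs 52% | 1.13 | 26% | 65% |
| 60% | 64% vs 68% | 1.06 | 15% | 48% |

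**The 50% figure in {21b}.** With *b* = 50% and 10% versus 25%, the count of a single condition is 55% and 62.5%, above 50% in both arms. New onset per randomized child is 5% and 12.5%.

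**The case against.** The strongest reply is that the article contains no scoring rule at all. A reader might infer that the plan ignores the 0 h value and scores a child whose platelet count is low at entry and rising. The documents do not support that. The side-effect item itself schedules haematocrit and platelets at baseline and an ECG before treatment, the timeline has glucose at 0 h, and no passage says that a prevalent or improving abnormality will be counted. This objection stands: the point concerns what the wording allows, not a stated mis-scoring.

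Further replies, and what is left of each:

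- *The 0 h mark may mean after randomization.* The 0 h column also holds allocation and the first dose, so the mark can be read consistently with the abstract. It is therefore an ambiguity to settle, not proof that pre-treatment events are counted.
- *Definitions of treatment-emergent events and grades are commonly left to a fuller document.* True, and silence alone would be a weak point. But the article does state an adverse event definition and an outcome label, and together they admit prevalent cases.
- *Randomization balances prevalent cases, and the absolute excess is not hidden.* Correct. No false difference between arms arises, and the risk difference per randomized child is unchanged. Its precision suffers, and the risk ratio, which the plan also reports, is attenuated.
- *The model fits the conditions unequally.* Glucose is measured every 6 hours and low values are corrected, so a later low value may often be a new episode. Section {11d} names severe anaemia and hypoglycaemia but not thrombocytopenia, and does not say that they are present at entry. Both remarks limit how large *b* may be for a given condition; neither supplies a rule.
- *A new-or-worse count keeps children abnormal at 0 h at risk of worsening.* The calculation does not model worsening, so the power of the proposed count is only approximated.

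**Conclusion.** The point holds in a conditional form. The protocol labels three conditions that severe malaria can itself produce as medication side effects and does not tie them to the entry values that it collects. As written, abnormality present at entry can be counted in both arms.

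If it is counted, the risk ratio moves towards 1 for any *b* above zero, power falls, and the stated rates overstate drug side effects. On the assumptions shown, the risk ratio falls from 2.5 to between 1.28 and 1.06 as *b* goes from 30% to 70%, and power from 95–65% (children normal at 0 h) to 64–20%. The percentage considered for early stopping could be inflated in the same way. None of these sizes can be derived from the documents; only the direction can.

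This is a secondary safety outcome and the primary survival comparison is untouched. The change is still worth making, because it sharpens the safety contrast with data already scheduled.

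**What to change.** 1. In Outcomes {12}, Secondary outcomes, count anaemia, thrombocytopenia and hypoglycaemia as side effects only when new or worse than the 0 h value by a prespecified grade.
2. Report abnormality present at 0 h as a baseline characteristic by arm.
3. Compare haematocrit and platelet count at 24 h and 48 h between arms with the 0 h value as covariate.
4. Reconcile the 0 h adverse event mark in the Participant timeline {13} with the post-randomization recording stated in the abstract, and make clear which count feeds the percentage in Interim analyses {21b}.

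All reporting of adverse events under {22} can stay as it is; only the derived outcome changes. A new-or-worse count will still include deterioration caused by malaria after randomization, and the comparison between arms is what addresses that part.

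Cost: wording, and one grading threshold per measure to fix in advance. No additional samples are needed. The stated side-effect percentages will be lower.

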### Eligibility criteria {10}

#### Inclusion criteria

Children between the ages of 6 months and 17 years as at the last birthday.Children with impaired consciousness (Glasgow Coma Scale < 11 for children older than 5 years or Blantyre Coma Scale < 3 children younger than 5 years) persisting for > 1 h after a seizure in the presence of demonstrable peripheral asexual *P. falciparum* parasitaemia. This is in line with the WHO guideline for malaria, 2021.

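### Self-reported adverse events and tinnitus are poorly fixed for children who enter unconscious and may be pre-verbal: widen the reporter and show how many were assessable

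*Protocol article*

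**What the plan says.** The Secondary outcomes section of the protocol article includes "The side effect profile (adverse events and serious adverse events) of medication in each arm of study". Within it, "solicited side effects include hypoglycaemia, arrhythmia, thrombocytopenia, tinnitus and anaemia", and the second class is "unsolicited adverse events as reported by patients post-randomization". No other reporter is named there.

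The Inclusion criteria admit "Children between the ages of 6 months and 17 years as at the last birthday" and require "Children with impaired consciousness (Glasgow Coma Scale < 11 for children older than 5 years", with a Blantyre Coma Scale threshold for younger children. Every participant therefore enters with impaired consciousness.

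The section on adverse event reporting and harms {22} is wider: "All participants in this trial will be monitored for medication side effects and adverse events", with every event entered on the case report form whatever its suspected cause. The Abstract and the Participant timeline {13} carry adverse-event recording through to day 29.

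Section {20a} has categorical outcomes compared between arms and "presented as risk differences, risk ratios, and 95% confidence intervals". Section {20c} adds "The result of the study will be analysed per protocol". No denominator for adverse events is written anywhere in the article.

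**The concern.** Four of the five solicited events can be found by glucose measurement, blood count or electrocardiogram. Tinnitus cannot: it is known only if the child says so. The unsolicited class, read literally, has the same dependence. Yet the named reporter is unconscious at entry and, at the youngest ages, unable to describe a symptom at any time.

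The article gives a rate by arm and names no assessable subset. The natural reading is therefore that a child with no report counts as a child with no event. A low tinnitus rate would then mix two things: children who did not have it, and children who could not say. Safety is part of the general objective, and quinine is the added drug, so the distinction matters. Recovery of consciousness and survival are themselves outcomes that the trial hopes will differ by arm, so the opportunity to report may differ too.

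**Working it through.** **Plan's own figure.** The article states no tinnitus or adverse-event rate, so there is none to reproduce on this point. The sample size does not depend on it. For 23.0% against 12.5%, two-sided 0.05 and 80% power, the pooled formula gives 207 per arm. That is 414 in total, and 414/0.90 = 460, close to the stated 470.

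**Passages side by side.** Under Secondary outcomes, unsolicited events come from the patient. Under {22}, all participants are monitored and all events recorded. Both cannot define the same data, because an event seen by a clinician in a comatose child is counted under the second and not under the first.

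**Effect of counting non-reporters as event-free.** Let p1 and p0 be the true risks in the dual and control arms, and r1 and r0 the shares able to report. Then:

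- reported risks are r1·p1 and r0·p0;
- the reported risk difference is r1·p1 − r0·p0, which equals r·(p1 − p0) when r1 = r0 = r;
- the reported risk ratio is (r1/r0)·(p1/p0), which equals the true ratio when r1 = r0.

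The illustration uses p1 = 30% and p0 = 5%. These are assumptions and are not in the documents. The true difference is 25.0 points and the true ratio 6.0.

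| r1 | r0 | Reported risks | Difference (points) | Ratio |
|---|---|---|---|---|
| 0.9 | 0.9 | 27.0% vs 4.5% | 22.5 | 6.0 |
| 0.7 | 0.7 | 21.0% vs 3.5% | 17.5 | 6.0 |
| 0.5 | 0.5 | 15.0% vs 2.5% | 12.5 | 6.0 |
| 0.3 | 0.3 | 9.0% vs 1.5% | 7.5 | 6.0 |
| 0.4 | 0.3 | 12.0% vs 1.5% | 10.5 | 8.0 |
| 0.3 | 0.4 | 9.0% vs 2.0% | 7.0 | 4.5 |
| 0.3 | 0.5 | 9.0% vs 2.5% | 6.5 | 3.6 |

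**A case using the article's planning figures.** Suppose that the 12.5% and 23.0% in Sample size {14} are deaths, that all of them occur without waking, and that no child is pre-verbal. Then r1 = 1 − 0.125 = 0.875 and r0 = 1 − 0.23 = 0.77. Absolute risks are understated by 12.5% and 23%, and the ratio is multiplied by 0.875/0.77 = 1.14. With the assumed risks above, 26.25% against 3.85% is reported: a difference of 22.4 points and a ratio of 6.8. The added drug then looks worse in relative terms and better in absolute terms. This is only an illustration. The section calls these figures reported outcomes, and the 23.0% belongs to quinine monotherapy, not to this trial's artesunate control.

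**The case against.** The strongest reply is that the error is inferred. No adverse-event denominator is written, section {20a} speaks of categorical outcomes in general, and {20c} promises to state the number with missing data, so a child who could not be asked might well be recorded as missing. Item-level denominators usually sit in the case report form or analysis plan, which are not shown. This stands: the whole-arm denominator is a natural reading and not a stated rule. It does not remove the point, because the article names a source of reports that does not fit its population and that its own section {22} contradicts.

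Second, coma is only the entry state. Recovery of consciousness is assessed at 12 and 24 h and events are recorded to day 29, so many children could wake and report later. This also stands. It does not help children who die without waking or who are too young to speak.

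A reader might infer more: that most of each arm cannot report, and that quinine's harm is therefore understated. The documents do not support either step. The first needs a reporting share below one half, and neither an age distribution nor a recovery rate is given. The second is secure only for absolute risks, and for the risk difference when the share is equal in both arms. The planned risk ratio is unaffected at equal shares, and faster waking or better survival in the dual arm would push it up, not down.

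Finally, section {22} largely covers unsolicited events that a clinician can see. What it cannot supply is a subjective symptom in a child who cannot speak.

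**Conclusion.** The point holds in limited form. The reporter named for unsolicited events does not suit a population that is unconscious at entry and includes infants, and it conflicts with the article's own wider monitoring rule. Tinnitus is listed with no provision for children who cannot be assessed.

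If such children are counted as event-free, absolute risks are too low by the fraction 1 − r, and so is the risk difference when r is equal between arms. The risk ratio is then correct, and with unequal r it can err in either direction. The actual size cannot be derived; the tinnitus risks and reporting shares used above are assumptions.

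The reach is narrow: one wholly subjective solicited item and the wording of one event class, within a secondary outcome. The primary outcome, the sample size and the objectively measured safety items are untouched. It is still worth correcting, because safety is in the general objective and the change is small.

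**What to change.** 1. Under Secondary outcomes, replace the patient-only source for unsolicited events with events observed by the clinician or reported by the caregiver or patient, in line with section {22}. Caregivers are already told of possible side effects at enrolment (section {11c}).
2. Record tinnitus as present, absent or not assessable. Ask at a fixed time in both arms, for example at the existing day-29 visit, with the question covering the period since randomisation.
3. Report the number assessable in each arm, and give tinnitus risk among children who regained consciousness and are above an age cut fixed in advance.
4. Label that comparison descriptive. The age cut is a baseline criterion, but regaining consciousness happens after randomisation and may depend on treatment, so the subset does not keep the protection of randomisation.

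The cost is one extra category on the case report form and a few words of text. The tinnitus denominator becomes smaller and its interval wider, and a question asked at day 29 relies on recall. No change to sample size or treatment is needed.
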